# Robot-assisted esophagectomy (RAE) versus conventional minimally invasive esophagectomy (MIE) for resectable esophageal squamous cell carcinoma: protocol for a multicenter prospective randomized controlled trial (RAMIE trial, robot-assisted minimally invasive Esophagectomy)

**DOI:** 10.1186/s12885-019-5799-6

**Published:** 2019-06-21

**Keywords:** Robot-assisted surgery, Thoracoscopic esophagectomy, Efficacy, Complications, Quality of life

## Abstract

**Background:**

Currently, there are three main surgical approaches for resectable esophageal cancer: open transthoracic esophagectomy (OTE), conventional minimally invasive esophagectomy (MIE) and robot-assisted esophagectomy (RAE). Previous studies had demonstrated the better short-term outcomes in MIE or RAE when compared to OTE, respectively. However, to date, no prospective study was designed to compare these two minimally invasive approaches (MIE and RAE). The primary objective of this study is to compare the outcomes on survival, safety and efficacy, quality of life between RAE and MIE in the treatment for resectable esophageal squamous cell carcinoma (ESCC).

**Methods:**

This study is designed as a multicenter, prospective, randomized, non-inferiority phase III clinical trial, investigating the safety and efficacy of RAE compared with MIE in the treatment of resectable ESCC. Eligible patients are randomly assigned to either RAE (*n* = 180) or MIE (*n* = 180) group. The follow-up visits will be scheduled at 3, 6, 9, and 12 months in the first two years, and then every 6 months until the end of the study. During the follow-up period, clinical data and quality of life questionnaires will be examined. The primary endpoint is the 5-year overall survival (OS). The secondary endpoints are 3-year OS, 5-year disease-free survival (DFS), short-term outcomes as well as quality of life.

**Discussion:**

This is the first prospectively randomized controlled trial designed to compare RAE with MIE as surgical treatment for resectable ESCC. According to our hypothesis, RAE will result in at least similar oncologic outcomes and long-term quality of life, but with a shorter operation time, lower percentage of perioperative complications, lower blood loss, and shorter hospital stay when compared with MIE. This study started in July 2017. Follow-up will terminate after 5 years from the time when the last patient was enrolled.

**Trial registration:**

ClinicalTrial.gov: NCT03094351 (March 29, 2017). The trial was prospectively registered.

## Background

Esophageal cancer is the seventh common malignant tumor and ranks sixth in tumor-related mortality worldwide in 2018. In terms of the histological subtypes, adenocarcinoma is frequently observed in Europe and the United States, while squamous cell carcinoma is the predominant form of Asian populations [1]. Although great advances have been made in the diagnosis and treatment of esophageal cancer, the overall 5-year survival only ranges from 15 to 25% [2]. Radical esophagectomy and lymphadenectomy has been widely acknowledged with paramount importance in cure-intended therapy for esophageal squamous cell carcinoma (ESCC).

Currently, there are three surgical approaches to perform a radical esophagectomy: open transthoracic esophagectomy (OTE), conventional minimally invasive esophagectomy (MIE) and robot-assisted esophagectomy (RAE). MIE is now the preferred surgical approach worldwide, which has brought better postoperative outcome by its minimally invasive feature [3, 4]. Besides, reduced morbidity and mortality rates have been reported when compared with the conventional open approach by previous studies [5, 6]. Apart from observational studies, there are several prospective trials demonstrated the advantages of MIE [7–9]. However, several problems still have not been solved. First, short-term outcomes were not obviously improved in esophageal cancer patients undergoing MIE [10]. Second, the oncological results of MIE remain to be proven, as no RCTs have demonstrated the long-term survival between MIE and OTE [11]. Third, several population-based studies have reported a higher re-intervention rate in patients who underwent MIE, while no evident reduction in postoperative complications or overall morbidity was observed [9, 12].

In 2003, RAE was developed at the University Medical Center Utrecht (UMCU) to overcome the technical limitations of MIE [13]. Based on the advantages of enlarged and three-dimensional view, RAE could facilitate the complex procedures in conventional thoracoscopic approach [14]. With the progress of robot technology during the past decade, RAE has become more popular in the surgical treatment for esophageal cancer [15, 16]. In terms of treatment outcomes, previously observational studies have shown that RAE is at least equivalent to OTE [17]. Up to date, prospective trials to compare RAE with OTE in the treatment of esophageal cancer are infrequent. The ROBOT trial was a randomized trial which aims to evaluate the safety and efficacy of RAE as an alternative technique to OTE for surgical treatment of esophageal cancer. The results demonstrated that RAE resulted in a lower incidence of postoperative complications and better quality of life when compared to OTE. Moreover, the two surgical techniques have comparable and satisfactory oncological results [18]. However, whether RAE can improve the outcomes and surpass the conventional MIE remains to be demonstrated.

To the best of our knowledge, no randomized studies were conducted to compare RAE with MIE in patients with resectable ESCC (cT_1-4a_N_0-2_ M_0_) to date. Hence, we launch this multicentric phase III prospective clinical trial to assess the potential advantages of RAE versus MIE in the surgical treatment for patients with ESCC.

## Objective

This is a multicenter, prospective, randomized, open and parallel controlled, non-inferiority trial, which aims to compare RAE versus MIE in the treatment for patients with ESCC.

## Methods

### Study design

This is a prospectively randomized controlled trial to assess the comparison between RAE and MIE in the treatment for patients with ESCC. According to previous studies, the long-term survival results of RAE seemed to be comparable but not inferior to the MIE or open esophagectomy [19, 20]. Therefore, the present study was designed as a non-inferiority trial, which was based on the hypothesis that the 5-year overall survival in the RAE is uncompromised with MIE. To achieve the primary goal, 360 patients with ESCC will be recruited from 4 high-volume centers (> 100 cases of combined approaches annually) in China. Based on the volume of esophagectomy in our center, 120 patients will be scheduled for this trial and approximately 5 patients will be enrolled for each group per month. For the other three centers, the estimated enrolled patients will be 2 for each group per month. The flow chart of this trial is presented in Fig. 1. The study has been approved by the ethics committees of participating institutions, as well as in accordance with the principles of the Declaration of Helsinki and Good Clinical Practice Guidelines. Written informed consent is obtained from each participant.

Neoadjuvant therapy will be used as a stratification factor in this study. After finishing preoperative treatment, patients will be restaged and confirmed to suitable for surgery by multidisciplinary team (MDT) of clinicians. When the tumor is considered as resectable, patients will undergo the randomized intervention - either RAE or MIE depending on randomization.

The study started on July 2017. Enrollment will take about 2 years and follow-up for will be 5 years. So the total duration of this study will lasts 7 years.

### Study population

Patients with thoracic ESCC will be considered as eligible for this trial. Investigators from each institution will take charge of the enrollment according to the inclusion/exclusion criteria and patients’ conditions.

### Inclusion criteria

Age ranges from 18 to 75 years;European Clinical Oncology Group Performance Status (ECOG PS) 0–2;Histological subtype of esophageal squamous cell carcinoma;Primary tumors are located at the intrathoracic esophagus;Pre-treatment stage as cT_1-4a_N_0-2_ M_0_ (AJCC/UICC 7th Edition);Didn’t receive any therapy including chemotherapy or radiation for other cancers;Written informed consent.

### Exclusion criteria

Cervical esophageal cancer and carcinoma of gastro-esophageal junction;Patients with unresectable or metastatic esophageal cancer;Histological subtype of esophageal non-squamous cell carcinoma;History of previous thoracic surgery;Patients with other malignant tumor (previous or current);Participation in another clinical trial during this study.

### Sample size considerations

The sample size was calculated based on the primary outcome overall survival. A non-inferiority trial is planned in which the primary analysis will use the non-inferiority log-rank test. Generally, non-inferiority margins in local-advanced cancers were in a narrow range (1.18–1.33) according to the FDA’s estimate [21]. After extensive discussion, the researchers have decided that the upper bound on non-inferiority is 1.33. The total trial will take about 7 years which consists of 2-year recruitment period and 5-year follow-up period. We estimated a missing rate of 5% per year in each group. A hazard rate of 0.60, a power of 0.80 and a significance level of 0.05 will be used. Based on the assumptions, a sample size of 360 (2 × 180) participants was calculated using PASS 11 software (NCSS, LLC; Version 11.0.7).

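### The sample size of 360 does not follow from its stated inputs, and the stated 80% power rests on a hazard that implies 5% five-year survival

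*Protocol article*

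**What the plan says.** Under Sample size considerations, "the primary analysis will use the non-inferiority log-rank test", and "the researchers have decided that the upper bound on non-inferiority is 1.33". The other inputs are "A hazard rate of 0.60, a power of 0.80 and a significance level of 0.05 will be used" and "We estimated a missing rate of 5% per year in each group". From these, "a sample size of 360 (2 × 180) participants was calculated using PASS 11 software".

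The horizon is given three times and consistently. The sample size section has "The total trial will take about 7 years which consists of 2-year recruitment period and 5-year follow-up period". Study design has "So the total duration of this study will lasts 7 years". The abstract's Discussion has "Follow-up will terminate after 5 years from the time when the last patient was enrolled".

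The section does not say whether 0.05 is one- or two-sided, what time unit the hazard of 0.60 has, or how many deaths are required.

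Two other sections carry survival figures. The Background gives an overall five-year survival of 15 to 25% for esophageal cancer. The main Discussion cites a retrospective comparison with five-year overall survival of 69% after RAE and 59% after MIE.

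**The concern.** The section prints nearly all the inputs of the calculation and presents 360 as their result, so the figure can be checked. It does not come out on either reading of alpha.

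The power of a log-rank test depends on the number of deaths, and the number of deaths depends on the hazard. At 0.60 per year almost every patient dies within the 7 years, so nearly all 360 count as events. If survival is anything like the figures quoted elsewhere in the article, there will be fewer deaths and the trial will have less than 80% power to show non-inferiority on its primary endpoint. A failure to show non-inferiority might then reflect too few deaths and say little about the operation.

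**Working it through.** **Inputs from the sample size section.** Margin 1.33; hazard h = 0.60; loss 5% per year; power 0.80; alpha 0.05; 2 years of accrual and 5 of further follow-up; 1:1 allocation.

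**Assumptions added.** True hazard ratio 1; hazard per year; exponential survival and loss; uniform accrual. Loss is entered as a hazard d = 0.05 or −ln(0.95) = 0.0513.

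**Step 1: deaths required.**
- Schoenfeld: 4(z_alpha + z_0.80)² / (ln 1.33)², with ln 1.33 = 0.2852.
  - One-sided 0.05: 4 × 2.4865² / 0.0813 = 304.1.
  - Two-sided 0.05: 4 × 2.8016² / 0.0813 = 386.0.
- Freedman: (z_alpha + z_0.80)² × (2.33/0.33)² = 308.2 and 391.3.

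**Step 2: probability that a death is observed, 2 + 5 years.** P = h/(h+d) × [1 − mean of exp(−(h+d)t)], with t uniform from 5 to 7 years. For d = 0.05 the mean is (e^−3.25 − e^−4.55)/(0.65 × 2) = 0.0217. So P = 0.9231 × 0.9783 = 0.903. With d = 0.0513, P = 0.901.

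**Step 3: patients required on the stated inputs.**
- One-sided: 304.1/0.903 = 336.7, up to 308.2/0.901 = 341.9. That is 337 to 342.
- Two-sided: 386.0/0.903 = 427.5, up to 391.3/0.901 = 434.1. That is about 427 to 434. The 386 to 391 deaths required already exceed 360 patients.

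Neither gives 360.

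**Step 4: power of 360 on the stated inputs.** Expected deaths: 360 × 0.903 = 325. Power = Φ(√325 × 0.2852/2 − z_alpha).
- One-sided: Φ(2.571 − 1.645) = 82%.
- Two-sided: Φ(2.571 − 1.960) = 73%.

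**Step 5: changes that would reach about 360 at one-sided 0.05.**
- Total time 5 years (t from 3 to 5): P = 0.848 to 0.850, N = 358 to 363.
- Total time 7 years, loss hazard 0.10: P = 0.843, N = 304.1/0.843 = 361.
- Total time 7 years, hazard 0.60/1.33 = 0.451 in both arms: P = 0.852 to 0.854, N = 356 to 362.

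**Step 6: the hazard against the article's own survival figures.** A hazard of 0.60 per year gives five-year survival e^−3.0 = 5.0% and a median of ln 2/0.60 = 1.16 years. With h = −ln(S₅)/5, the stated 7 years, d = 0.05, one-sided 0.05 and Schoenfeld deaths:

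| Five-year survival | Where quoted | h per year | P(death observed) | Deaths in 360 | Power of 360 |
|---|---|---|---|---|---|
| 5% | implied by 0.60 | 0.600 | 0.903 | 325 | 82% |
| 15% | Background | 0.379 | 0.814 | 293 | 79% |
| 25% | Background | 0.277 | 0.726 | 261 | 75% |
| 59% | Discussion, MIE | 0.106 | 0.411 | 148 | 53% |
| 69% | Discussion, RAE | 0.074 | 0.313 | 113 | 45% |

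Freedman's formula lowers these powers by up to half a percentage point.

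**The case against.** The strongest reply is that the discrepancy is harmless. At one-sided 0.05 and the stated hazard, 360 is some 20 patients more than needed and gives 82% power against a stated 80%. Rounding up cannot be excluded. This stands as far as it goes, but it needs the one-sided reading, which the article does not state, and it needs the 0.60 hazard.

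A reader might infer that the 5-year follow-up was entered in the software as the total study time, because a 5-year total gives about 358 to 363. The documents do not support treating this as fact. They state 7 years throughout and mention no 5-year total. The exact match to 180 per arm needs one particular pairing of formula and loss hazard, and Step 5 shows two other single changes that fit about as well with 7 years kept. A reader might also infer that a horizon error will grow once the hazard is corrected. That would happen only if a recalculation used 5 years despite the stated 7. It would then overstate the required number, which is again the safe direction.

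The survival benchmarks can be questioned too. The Background range is for esophageal cancer overall, and 59% and 69% come from one retrospective comparison. Neither is a firm estimate for this population, so the table shows a range and does not forecast. Even so, every figure the article quotes lies well above 5%.

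Finally, the unit of the hazard is not stated. If 0.60 were the cumulative hazard over five years (0.12 per year), survival would be e^−0.6 = 55%, which is plausible. But then P = (0.12/0.17) × [1 − (e^−0.85 − e^−1.19)/0.34] = 0.450 and N = 304.1/0.450 = 676, so that reading does not produce 360 either.

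**Conclusion.** The point holds in two parts of unequal weight.

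- **The printed number.** 360 is not the result of the printed inputs on either reading of alpha. If one-sided, the error is about 5 to 6% and conservative. If two-sided, the trial is short by about 67 to 74 patients on its own inputs. The cause cannot be identified from the article.
- **The power claim.** The stated 80% power fails mainly because of the hazard. Against the article's own survival figures, the shortfall over the stated 7 years at one-sided 0.05 runs from slight (75 to 79%) to severe (53% and 45%).

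These results assume a true hazard ratio of 1, exponential survival and loss, uniform accrual and a hazard per year. The choice of event formula or loss hazard changes the required size by a few patients and does not alter the conclusion.

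**What to change.** Keep the planned enrolment of 360 and correct the paragraph:

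1. Rerun the calculation with accrual 2 and total time 7, and report those entries.
2. Use a hazard consistent with the survival figures the article quotes, with its unit and source. Show a range if the source is uncertain.
3. State whether 0.05 is one- or two-sided.
4. State the required deaths (304 to 308 if one-sided, 386 to 391 if two-sided), the deaths expected from 360 patients and the power they give.

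The cost is one software run and a rewritten paragraph. The article reports 210 patients recruited by 1 December 2018 with recruitment still open, so the correction can be on record well before the five-year survival analysis. The downside is that the restated power may be less favourable than 80%.

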### Randomization

Randomization will be performed via a computer-generated random numbers sequence and further stratified by whether the patient has undergone neoadjuvant treatment or not. Considering the unfeasibility in clinical practice, no blinding will be set for the patients and surgeons. Nevertheless, the independent study team is blinded to the allocation.

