### Surgical technique

All patients underwent RAE or MIE (McKeown procedure) with two-field lymphadenectomy by the same experienced surgeons who had entirely completed the learning curve in each center. A surgeon who accomplished 40 cases of RAE or MIE annually is determined to be sufficiently skilled for our study. RAE is completed using Da Vinci surgical system (Intuitive Surgical, Inc., Sunnyvale, CA, USA) and MIE is carried out with a thoracoscopic-laparoscopic system.

For RAE, the procedure in details has been described in our previous article [22]. For the thoracic phase, patients are placed in the left semi-prone position and trocars arrangement are presented in Fig. 2a. The mediastinal pleura above the arch of the azygos vein is divided firstly. Lymph nodes along the right-RLN and the superior esophagus are dissected en bloc. Then the dissection continued from the right main bronchus up to the plane between the esophagus and the trachea membrane. Lymphadenectomy is performed along the left-RLN from the thoracic outlet to the aortic-pulmonary window. The subcarinal lymph nodes will be dissected after this step, and the lower esophagus is dissected to the hiatus. For the abdominal phase, patients are placed in the reverse Trendelenburg position, and the robotic cart will be docked from the head side of the patient. Five ports are used in the abdominal stage, including one observation port, two robotic arm ports and two assistant ports (Fig. 2b). The greater curve is dissected firstly until the short gastric artery. The celiac area is dissected and the left gastric artery is cut off. Then the operation converts to the hepatogastric ligament, in which the right crus, left crus as well as fundus are dissected. A small incision is made at the sub-xiphoid and a narrow gastric tube (3–4 cm) will be made from the abdomen. Finally, the anastomosis is completed at the neck.

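### Neoadjuvant treatment is the only named stratification factor; leaving centre out of a four-centre surgical trial adds avoidable chance imbalance, though not bias

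*Protocol article*

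**What the plan says.** The Randomization section of the protocol article describes the scheme in one sentence: "Randomization will be performed via a computer-generated random numbers sequence and further stratified by whether the patient has undergone neoadjuvant treatment or not". The Study design section agrees: "Neoadjuvant therapy will be used as a stratification factor in this study". Neither section names centre as a stratum, a blocking unit or a minimisation factor, and no other section does.

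The Study design section also sets out the multicentre structure: "360 patients with ESCC will be recruited from 4 high-volume centers (> 100 cases of combined approaches annually) in China". For the lead centre it plans that "120 patients will be scheduled for this trial and approximately 5 patients will be enrolled for each group per month". It then adds: "For the other three centers, the estimated enrolled patients will be 2 for each group per month". Recruitment is thus expected to be equal between groups within each centre, and unequal between the lead centre and the rest.

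The Surgical technique section says that both operations are done "by the same experienced surgeons who had entirely completed the learning curve in each center". The Randomization section makes the trial open to patients and surgeons. The Statistical analysis section lists an overall log-rank test, t test or ANOVA, and chi-squared or Fisher tests, without mentioning centre. The Current status section reports 210 patients recruited by 1 December 2018.

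**The concern.** The intervention is an operation, and each centre supplies its own surgeons. Centre is therefore a natural carrier of differences in operator, case mix and local practice. Allocation that ignores centre can leave the arms uneven within a centre by chance, and any real difference between centres then enters the unadjusted treatment comparison.

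Two kinds of outcome are exposed. The first is overall survival, judged against a margin where "the upper bound on non-inferiority is 1.33". The second is the set of short-term outcomes that depend on local routine, such as hospital and ICU stay, drain removal, oral intake and complications. Having the same surgeons do both operations controls for centre and surgeon most fully when the arms are balanced within each centre, and the published scheme does not provide for that.

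**Working it through.** **Inputs from the article.** Total 360, allocated 180:180 (Sample size considerations: "a sample size of 360 (2 × 180) participants was calculated using PASS 11 software"); four centres; 120 patients at the lead centre; equal monthly rates at the other three; margin 1.33.

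**Assumptions.** The remaining 360 − 120 = 240 patients divide equally, 80 per centre. This fits the stated rates: 2 × 2 = 4 patients a month gives 80 in 20 months, inside the planned two-year enrolment. The 1.5-fold hazard used below is also assumed.

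**The plan's own figure.** The article gives no figure for balance within centres, so there is none to reproduce on this point. The sample size is needed only for scale. With one-sided 0.05 and power 0.80, the events required are 4 × (1.645 + 0.842)² / (ln 1.33)² ≈ 305. Reading the hazard of 0.60 as per year, with 5% yearly loss, the event probability is 0.901, so N = 339; a further division by 0.95 gives 357, close to 360. The sidedness and the time unit are my readings. At 305 events the SE of the log HR is 2/√305 = 0.115, and the margin on the log scale is ln 1.33 = 0.285.

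**Step 1: split in one 80-patient centre, arms balanced 180:180 overall.** The number allocated to RAE is hypergeometric(360, 180, 80).
- Variance = 80 × 0.5 × 0.5 × (360 − 80)/(360 − 1) = 15.6, so SD = 3.95.
- 95% range: 32 to 48.
- Chance of 48:32 or worse, in either direction, in one named centre: 5.7%. In the direction that puts more patients on RAE: 2.8%.

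**Step 2: at least one of the three 80-patient centres.** Simulation of the joint allocation gives:
- 46:34 or worse: 0.39.
- 48:32 or worse: 0.15.

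**Step 3: simple randomisation.** With binomial(80, 0.5), the chance of 48:32 or worse is 0.093 per centre. For any of three it is 1 − (1 − 0.093)³ = 0.25.

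**Step 4: all four centres, by simulation.** The chance that at least one centre is 60:40 or worse is about 28% with simple randomisation and about 16% with blocks of 4 inside the two neoadjuvant strata only. Assuming a neoadjuvant share of 20% or 50% makes almost no difference.

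**Step 5: effect on the overall survival hazard ratio.** Let one 80-patient centre have a hazard 1.5 times the others. With *a* of its patients on RAE, the approximate shift in the crude log HR is [(2*a* − 80)/180] × ln 1.5.
- SD of the shift = (2 × 3.95/180) × 0.405 = 0.018.
- Share of the variance of log HR: 0.018²/0.115² ≈ 0.02, about 2%.
- If that same centre happens to split 48:32: (16/180) × 0.405 = 0.036, an HR factor of 1.037. This is 13% of ln 1.33 (0.036/0.285) and 0.31 of the SE (0.036/0.115).
- If instead the 120-patient lead centre differs by a factor of 1.25, 1.5 or 2.0, 95% of chance shifts lie within HR factors of about 0.98–1.02, 0.96–1.04 and 0.93–1.07.

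**Step 6: what stratifying by centre would give.** With 4 × 2 = 8 strata and blocks of 4 (assumed) from the start, the arms differ by at most 2 per stratum and so by at most 4 per centre. The worst split would be 42:38 in a centre of 80 and 62:58 in the centre of 120.

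**The case against.** **The wording is not exclusive.** The article calls neoadjuvant therapy a stratification factor and never says it is the sole one. List structure and blocks are details that a condensed article may leave to the full protocol. This stands in part: lists may have been kept by centre. But the article describes the scheme twice and names one factor both times, so the fair reading is that centre is not part of it as published. An analysis plan could adjust for centre, but it would not alter how patients are allocated.

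**Differences between centres are inferred.** No section says that skill, care or case mix differ. The article points partly the other way: all four centres are high-volume, and the surgeons have passed their learning curve. This stands, and so the hazard ratios between centres above are labelled as assumptions.

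**Stronger readings that a reader might infer.**
- *That the treatment comparison is biased.* It is not. The imbalance is random and equally likely in either direction.
- *That an imbalance would break a planned within-centre comparison.* The article plans no such comparison; it says only that the same surgeons do both operations. A 48:32 split would in any case keep 4 × 0.6 × 0.4 = 96% of the efficiency of 40:40.
- *That the 15% chance goes with the 1.04 shift.* It does not. The 15% is for any of three centres, whereas the shift needs one particular centre to be both split 48:32 and at the assumed higher hazard. For a named centre the chance is 5.7%.
- *That the per-centre recruitment figures contradict the allocation scheme.* They are estimates and not guarantees, so this is a weak design choice and not an inconsistency.

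**The change comes late.** With 210 of 360 already recruited, new strata cannot rebalance them, and eight strata for 150 patients average under 19 each. This stands, and is why the remedy must also reach the analysis.

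**Conclusion.** The point holds as a design weakness of modest size. As published, allocation is stratified by neoadjuvant treatment alone, and nothing described secures balance within four centres that have their own surgeons and unequal recruitment. A split of 48:32 or worse in at least one of the three smaller centres has a probability of about 15% to 25%, depending on whether the overall totals are balanced and on the assumed 120/80/80/80 sizes.

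For the primary endpoint the cost is small: about 2% of the variance of the log HR if one 80-patient centre has an assumed 1.5-fold hazard. For stay, drain days and complications a larger effect is plausible because they depend on local practice, but the article gives nothing from which to size it. The change is worth making because the noise is cheap to avoid; the validity of the trial does not depend on it.

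**What to change.** 1. For the patients still to be allocated (360 − 210 = 150 at the reported status date, and fewer by the time of any amendment), stratify by centre as well as neoadjuvant treatment, through a central system with concealed, randomly varying block sizes.
2. Because the patients already allocated cannot be rebalanced, include centre with neoadjuvant treatment as a stratum or covariate in the primary overall survival analysis and in the analyses of short-term outcomes. If an analysis plan already does this, a cross-reference is enough.
3. Report the number allocated to each arm by centre.
4. If lists were in fact kept by centre, state this in the protocol; item 1 then falls away.

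Cost: a short amendment and a revised randomisation list, with no extra patients or visits. The drawback is that blocks within a centre make the next allocation somewhat easier to guess in an open trial. Varying and concealing the block sizes limits this but does not remove it.

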### Statistical analysis

Statistical analyses are performed using SPSS version 20.0 software (SPSS Inc. Chicago, Illinois, USA). Survival will be estimated by Kaplan-Meier methods and analyzed using log-rank test. Complications will be calculated as percentage with 95% confidence intervals and analyzed by χ^2^ test or Fisher’s exact test. Student’s *t* test and analysis of variance (ANOVA) test was conducted for the comparison in continuous variables, while χ^2^ test or Fisher’s exact test was used in categorical variables. *P* < 0.05 is set as the significance level.

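### Randomisation is stratified by neoadjuvant treatment, but none of the named tests uses that stratum; if it is prognostic, the unstratified survival comparison leans towards non-inferiority

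*Protocol article*

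**What the plan says.** Two places set the randomisation. Under Study design: "Neoadjuvant therapy will be used as a stratification factor in this study". Under Randomization, the computer-generated sequence is "further stratified by whether the patient has undergone neoadjuvant treatment or not". No other factor is named. The trial has several sites ("360 patients with ESCC will be recruited from 4 high-volume centers"), but centre is not a stratum.

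Two places set the analysis. Under Sample size considerations, "the primary analysis will use the non-inferiority log-rank test", with an HR margin of 1.33. Under Statistical analysis:

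- Survival: "Survival will be estimated by Kaplan-Meier methods and analyzed using log-rank test".
- Complications: "Complications will be calculated as percentage with 95% confidence intervals", compared by chi-square or Fisher's exact test.
- Continuous outcomes: Student's t test and "analysis of variance (ANOVA) test was conducted for the comparison in continuous variables".

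No test is described as stratified or adjusted, and no Cox model or HR estimator is named.

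**The concern.** An analysis should normally follow the randomisation. Here the design fixes one stratum and the named tests leave it out.

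For survival the loss is not only one of precision. Leaving out a prognostic factor pulls an HR other than 1 towards 1. In a superiority trial that is conservative. In this trial the error to guard against is declaring non-inferiority when the true HR is 1.33, and attenuation makes that error more likely.

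For complications, operating time, blood loss and similar outcomes, only precision is at stake.

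**Working it through.** **Inputs from the article.** Margin 1.33; N = 360, 1:1; hazard 0.60 (unit not stated, read as per year); loss 5% per year; 2-year accrual plus 5-year follow-up; power 0.80; alpha 0.05 (sidedness not stated).

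**Assumed, because the article is silent.** Stratum HR of 1, 1.5, 2 or 3; half of the patients in each stratum; exponential survival.

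**Step 1: the plan's own figure.** Schoenfeld events at one-sided 0.05: 4 × (1.645 + 0.842)² / (ln 1.33)² = 4 × 6.18 / 0.0813, about 305.

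Event probability with h = 0.60, loss 0.05 and uniform 2-year accrual over 7 years: (0.60/0.65) × [1 − (e^(−3.25) − e^(−4.55)) / (0.65 × 2)] = 0.923 × 0.978 = 0.903.

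This gives N = 305/0.903 = 338, or 338/0.95 = 356. A 5-year total duration gives p = 0.850 and N = 359. So 360 is reproduced within 3% as a one-sided 0.05 design. A two-sided 0.05 needs 387 events and does not reproduce it (429 or more patients). The one-sided reading is used below. The calculation contains no stratum.

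**Step 2: simulation at the margin.** True within-stratum HR 1.33, N = 360, arms balanced within strata, 8,000 runs per scenario (Monte Carlo SE about 0.0024 at an error of 0.05).

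| Event rate | Stratum HR | HR unstratified / stratified | One-sided error unstratified / stratified |
|---|---|---|---|
| 0.60 per year | 1.0 | 1.331 / 1.331 | 0.046 / 0.048 |
| 0.60 per year | 1.5 | 1.320 / 1.332 | 0.055 / 0.051 |
| 0.60 per year | 2.0 | 1.299 / 1.331 | 0.069 / 0.050 |
| 0.60 per year | 3.0 | 1.267 / 1.331 | 0.090 / 0.049 |
| 5-year OS about 60% | 1.0 | 1.331 / 1.331 | 0.055 / 0.056 |
| 5-year OS about 60% | 1.5 | 1.330 / 1.334 | 0.050 / 0.048 |
| 5-year OS about 60% | 2.0 | 1.322 / 1.335 | 0.047 / 0.046 |
| 5-year OS about 60% | 3.0 | 1.303 / 1.332 | 0.054 / 0.051 |

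A separate simulation of the stratum HR 2 case at 0.60 per year gave 0.064. At the lower event rate, the scenario with no stratum effect itself gives 0.055 and 0.056, so the differences there are within noise.

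**Step 3: check by hand.** At 0.60 per year and stratum HR 2 there are about 324 events, so the SE of the log HR is 2/√324 = 0.111. The shift is ln(1.33/1.299) = 0.0236, or 0.21 SE. The error is then about Φ(−1.645 + 0.21) = 0.076. This is a little above the simulated value, as expected: balance within strata makes the unstratified statistic vary less than 2/√events implies.

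**Step 4: true HR of 1.** Both analyses return an HR of 1.00. At 0.60 per year, power is 0.82 to 0.83 unstratified and 0.79 to 0.82 stratified; the 0.79 belongs to stratum HR 3.

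**Step 5: which event rate applies.** A hazard of 0.60 per year implies a 5-year OS of e^(−3.0), about 5%. The Background gives 15 to 25% for oesophageal cancer overall, and the Discussion cites 59% for MIE. The first block of the table is therefore the high end of the range. Rates in between were not simulated.

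**Step 6: binary and continuous outcomes.** With arms balanced within strata, the raw difference in means or proportions is unbiased. For a mean, the unadjusted SE includes the between-stratum variance and is too large by a factor of 1/√(1 − R²), where R² is the share of outcome variance that the stratum explains. The article gives no R². The test is conservative, not biased.

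**The case against.** The strongest reply is that the article is silent and does not rule stratification out. It is condensed, the analysis plan is not shown, and a log-rank test can be stratified just as an ANOVA can carry a factor. A reader might infer that the sponsor has decided on unstratified tests; the text does not go that far. What remains is that the article reports the stratification twice and names the tests twice without connecting them, and as named the tests are the unstratified ones.

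Second, 1.33 is not defined as a within-stratum HR, and the sample size uses one hazard without strata. Part of the attenuation is thus a change of estimand, and calling it bias presumes the within-stratum HR is the target. That is fair. It is a reason to state which HR is compared with 1.33.

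Third, attenuation needs a prognostic stratum and a true HR other than 1. The article quantifies neither the stratum's effect nor its prevalence. This stands in full.

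Fourth, a reader might infer that leaving out centre is also an error. It is not: centre is not a randomisation stratum, so omitting it contradicts nothing. Chance imbalance between centres is already covered by the standard error.

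**Conclusion.** The point holds in limited form. The only randomisation stratum is missing from every named test. For OS the consequence runs in the unwanted direction, provided that neoadjuvant treatment is prognostic and the true HR exceeds 1.

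Under the assumed stratum HRs of 1.5 to 3 and a 50:50 split, one-sided error is about 0.055 to 0.09 at 0.60 per year, against about 0.05 when stratified. At a 5-year OS near the 59% cited in the Discussion, inflation is negligible. Neither the stratum effect nor the split comes from the article, so no single figure can be claimed.

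Two stronger readings are not supported. The HR is not pulled towards 1 unconditionally: there is no shift at a true HR of 1 or with a stratum that is not prognostic. The chi-square and t tests are not biased either; they estimate no HR and lose only some precision.

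**What to change.** State that OS is compared with 1.33 by a log-rank/Cox analysis stratified by neoadjuvant treatment (yes/no), as at randomisation. Use the upper confidence limit that matches whichever sidedness of alpha the sponsor confirms. Analyse DFS the same way, and report the unstratified OS result as a sensitivity analysis.

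For secondary outcomes, adjust for neoadjuvant treatment: Mantel-Haenszel or logistic regression for complications and other binary outcomes, a linear model for continuous ones. Centre may be added for precision, but this is optional.

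The cost is analysis wording only. Neoadjuvant status must be known in order to randomise, so no new data are needed, and N stays at 360. At 0.60 per year, power changes from 0.82–0.83 to 0.79–0.82, falling just below the planned 0.80 only at the assumed stratum HR of 3. The change should be fixed before OS is analysed by arm.
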